3.3 Privacy and confidentiality

3.4 Conflict of interest

3.5 Publication policy

3.6 Termination of study

**4.0 Gantt Chart and Milestone**

**5.0 Budget**

**6.0 References**

**7.0 Appendices**

## **Abstract**

### **Background**

Prehabilitation often referred to as a fit-for-surgery program in the form of body conditioning exercises aims to optimize the patient's condition before surgery. However, the precise protocol of prehabilitation has not been completely established.

### **Objective**

This study aims to (i) develop prehabilitation of intensity training protocol and (ii) evaluate the potential effects of high-intensity interval training (HIIT) compared to moderate intensity continuous training (MICT) among patients undergoing major abdominal surgery.

### **Methods**

A two-phase research design will be executed: (i) the first phase is a cross-sectional web survey will be conducted to explore the current practice amongst physiotherapists treating patients following major abdominal surgery in Malaysia hospitals and eventually develop a protocol for prehabilitation program; and (ii) the second phase will be a prospective, double-blinded randomized controlled trial (RCT) which aims to determine the potential effect of HIIT on multi-domain recovery. For the web survey, 74 Malaysian physiotherapists will be recruited to complete this survey. For the RCT, a total of 70 participants will be recruited from the surgery and anaesthetic clinic at the Hospital Canselor Tunku Muhriz. Participants will be randomly allocated to either receive HIIT or MICT (control group) with 35 participants in each group. Both groups will receive body conditioning and respiratory muscle strength exercises. For the intervention group, participants will receive HIIT and the control group MICT. This will be one-hour therapist-supervised intervention sessions for at least 4 weeks of exercise duration with 2 sessions per week before the surgery. The patient will be assessed at baseline, before the operation, before discharge and 4 weeks postoperatively and 3 months postoperatively. The outcomes will be assessed using multi-domain recovery measures that include physical measures (6MWT), Short Physical Performance Battery and 1 minute Sit to Stand), upper limb strength (Hand Grip Test), fatigue (Fatigue Severity Scale), psychological recovery (the Hospital Anxiety Depression Scale (HADS) and health-related quality of life (EuroQoL). Data will be analysed using intention-to-

treat analysis. The changes from all timelines in the secondary outcomes will be analysed using the Mixed Model ANOVA test.

**Result:** The findings of this research will inform guidelines of prehabilitation in determining the optimal dosage of exercise prescriptions/intensity for patients undergoing major abdominal surgery.

**Conclusion:**

The protocol of this study is registered in the Australia New Zealand Clinical Trial Registry with registration number ACTRN12625000023459.

**Keywords :** Major abdominal surgery, prehabilitation, body conditioning exercise, high intensity interval training, moderate intensity exercise training

## **Introduction**

Abdominal surgery is the most common surgery performed worldwide [1]. Elective major abdominal surgery (MAS) is defined as a planned of any abdominal surgery where the total incision length is  $\geq 5$  cm involving open, laparoscopic, or minimally invasive procedures performed under general anaesthesia, with an incision into the abdominal cavity, visceral manipulation, and at least an overnight hospital stay [1].

The most common complication following MAS is a postoperative pulmonary complication (PPCs) with a reported incidence of 13–53 % [2]. Most PPCs manifest within the initial 3 days following surgery [3,4]. Evidence indicates that PPCs are associated with prolonged hospital stays [5,6], an elevated risk of unplanned readmissions [5], diminished quality of life and physical function [7], and an increased risk of all-cause mortality within 12 months [2,5]. Owing to the high incidence of PPCs and their substantial impact on patients, the prediction and targeted prevention of PPCs are strongly recommended [8].

Enhanced Recovery after Surgery (ERAS) is an evidence-based preoperative, intraoperative and postoperative multi-model care pathway that aims to reduce stress response to surgery and accelerate post-op recovery through enhancing patient mobilization, reducing complication rates after surgery, decreasing hospital length of stay and reducing healthcare costs [1,9,10]. Since ERAS was first implemented within hospitals over twenty years ago, post-surgical outcomes have improved for patients [11]. Length of stay has decreased, with no subsequent increase in readmission rates [12], with concurrent improvements in clinical outcomes whilst having a beneficial impact on healthcare resources. ERAS originated in elective colorectal surgery but has spread to other surgical subspecialties, including, but not limited to, gastrointestinal, hepatobiliary, orthopaedic, cardiac, thoracic, head and neck, breast and gynaecologic surgery [13]. The ERAS approach comprises preoperative, intraoperative, and postoperative components, with optimization of the patient's physical status before surgery as a key focus [9]. Therefore, prehabilitation program by physiotherapists is essential in enhancing patients' recovery and improving their outcomes after surgery including physical performances, psychological and health related quality of life [2,14,15].

The role of physiotherapy within ERAS pathways is important in both preoperative and postoperative routines [16]. Implementing a preoperative strength programme has been shown to

promote musculoskeletal improvements in preparation for a forthcoming physiological stressor, and is an emerging key component of ERAS [16]. A literature review found preoperative exercise in patients scheduled for cardiovascular, thoracic, abdominal and major joint replacement surgery to be well-tolerated and effective [17]. Postoperative exercise programmes are also recommended by ERAS guidelines, promoting muscle hypertrophy and the return to function after major surgery [18].

The standard prehabilitation program may include aerobic exercise which often moderate-intensity continuous training (MICT) is used to improve cardiovascular fitness [29], resistance training to strengthen muscles and improve overall physical function [16], breathing exercise to enhance lung capacity and respiratory muscle strength [20], and education with lifestyle counselling includes guidance on smoking cessation, nutrition, and overall physical activity [21]. High-intensity interval training (HIIT) is a bolus-dosing approach that efficiently increases cardiorespiratory fitness (CRF) and is feasible in most surgical populations. High-intensity interval training involves repeated aerobic high-intensity intervals at approximately 80% of the maximum heart rate, followed by active recovery [22,23,24]. The rapid increases in CRF elicited with HIIT is appealing for preoperative patients, and in the context of pathology, age, and comorbidities, the volume of training stimulus required to improve CRF can often be achieved [24].

HIIT provides advantages in terms of time efficiency, greater cardiorespiratory fitness, improved metabolic health and more effectiveness in preserving muscle mass. Studies demonstrated that HIIT, required significantly less time than MICT, produced similar cardiovascular and metabolic health improvements [25,26,27]. The study highlighted the time efficiency of HIIT as a major advantage for patients with limited time before surgery. The study by Weston et al. (2014) showed that HIIT led to greater improvements in  $VO_2$  max compared to MICT in patients with cardiovascular disease [28]. Given that  $VO_2$  max is a key indicator of cardiorespiratory fitness, HIIT's superior outcomes highlight its potential benefit in prehabilitation [28].

The current literature highlights the significant impact of prehabilitation on improving patient outcomes in the context of major abdominal surgery. Prehabilitation programs incorporating aerobic, resistance, and breathing exercises, alongside education and lifestyle counselling, have been shown to enhance cardiorespiratory fitness, reduce postoperative complications, and expedite recovery. While moderate-intensity continuous training (MICT) is

commonly used in such programs, high-intensity interval training (HIIT) has emerged as a time-efficient and potentially superior alternative, particularly in improving VO2 max and preserving muscle mass.

Despite these findings, there is a lack of standardized exercise protocols tailored to the prehabilitation phase for patients undergoing major abdominal surgery. Additionally, limited data exist on the health status and functional outcomes of these patients throughout the surgical timeline. This gap warrants further investigation into the comparative effectiveness of HIIT and MICT, particularly in terms of their impact on multidomain recovery. By addressing these research gaps, this study protocol aims to provide valuable insights into optimizing prehabilitation strategies, ultimately improving the quality of care and recovery outcomes for patient

s undergoing major abdominal surgery.

Therefore, this study intended to evaluate the effectiveness of HIIT over MICT prehabilitation training on cardiorespiratory fitness and maximum inspiratory pressure among patients undergoing major abdominal surgery. This study also aims to investigate the effectiveness of HIIT versus MICT prehabilitation training on physical performances, upper limb strength, body composition, fatigue, psychological and health-related quality of life. We hypothesize that a 4-week HIIT program during prehabilitation is non-inferior to MICT in improving the targeted outcomes following major abdominal surgery, meaning the difference between the two interventions does not exceed the pre-specified non-inferiority margin ( $\Delta$ ).

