## **1.3. Objectives**

### **Primary Objective**

To determine the effect of HIIT over MICT on physical performance which is cardiorespiratory fitness (6MWT) and maximum inspiratory pressure among patients undergoing major abdominal surgery.

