#### **1.4 Hypothesis**

- i. There will be variations in the standard of practice to these key questions across different states in Malaysia and among Malaysian physiotherapists in treating patients undergoing major abdominal surgery.
- ii. HIIT is non-inferior to MICT in improving cardiorespiratory fitness, maximum inspiratory pressure, physical performance, upper limb strength, body composition, fatigue, psychological recovery and health-related quality of life

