#### **Phase 2: RCT Comparing HIIT vs. MICT**

The randomized controlled trial (RCT) in Phase 2 will test the effectiveness of High-Intensity Interval Training (HIIT) compared to current standard of care (which will likely resemble the practices identified in Phase 1, i.e., MICT). This phase aims to demonstrate whether a change in the type of prehabilitation exercise improves multidomain recovery, including functional capacity, postoperative complications, and quality of life.

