## **Sampling and Size Calculation**

The sample size was calculated based on the primary outcome measure (6MWT). A recent systematic review of prehabilitation in patients undergoing major abdominal surgery reported significant improvement in 6MWT, with a mean difference of 29.4 meters (95% CI: 5.6 to 53.3 meters;  $p = 0.02$ ) compared to standard care [31]. The estimated standard deviation was approximately 101.6 meters, corresponding to an effect size (Cohen's  $d$ ) of 0.29. Using this effect size, with  $\alpha$  of 0.05 and power of 80%, the required sample size was calculated to be 54 participants. Allowing for a 30% dropout rate, a total of 70 participants (35 per group) will be recruited. Sample size calculation was performed using G\*Power version 3.1.9.7.

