The level of significance is set at  $p < 0.05$ . Effect sizes will be determined using Cohen's  $d$ , with values of 0.2, 0.5, and 0.8 indicating small, medium, and large effects, respectively [62]. Additional logistic regression will be used to determine preoperative, perioperative and postoperative risk factors associated with the development of respiratory complications. This will be an exploratory analysis, which may identify trends of predictors reported in the literature having an individual effect on postoperative respiratory complications. For all tests conducted, a  $p$  value of  $< 0.05$  (two-sided) will be considered statistically significant, and mean differences (95% CI) will be reported. The results of this study will be reported in accordance with the CONSORT 2010 guidelines.

|                                                                  | STUDY PERIOD                   |                                 |              |                                     |                                               |                                   |                              |
|------------------------------------------------------------------|--------------------------------|---------------------------------|--------------|-------------------------------------|-----------------------------------------------|-----------------------------------|------------------------------|
|                                                                  | Enrolment
& allocation      | Baseline                        | Intervention | Post-
intervention
assessment | Follow up                                     | Follow up                         | Follow up                    |
| TIMEPOINT                                                        | February
2025- July
2026 | 3-5 week
before
operation | 2- 4 weeks   | Preoperatively                      | Post-
operatively
prior to
discharge | 4-6 weeks
post-
operatively | 3 months post
operatively |
| Eligibility screen                                               | X                              |                                 |              |                                     |                                               |                                   |                              |

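### The non-inferiority hypothesis rests on a margin with no stated value, while the objective, sizing and analysis are built to detect a difference, so no planned rule tests it

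*Protocol*

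**What the plan says.** **Hypothesis.** The Introduction hypothesises that a 4-week HIIT programme is non-inferior to MICT, in the sense that the difference "does not exceed the pre-specified non-inferiority margin", followed by the symbol Delta. Section 1.4 repeats it as the formal hypothesis: "HIIT is non-inferior to MICT in improving cardiorespiratory fitness, maximum inspiratory pressure, physical performance", and further named domains.

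**Margin.** No value in metres, cmH2O or scale points appears in the objectives, outcome, sample size or analysis sections. The only other Delta, in the Phase 1 survey calculation, is a confidence-interval width for a proportion.

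**Objective.** The primary objective is "To determine the effect of HIIT over MICT on physical performance which is cardiorespiratory fitness (6MWT) and maximum inspiratory pressure". The Phase 2 description asks "whether a change in the type of prehabilitation exercise improves multidomain recovery". Both are difference questions.

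**Sizing.** "The sample size was calculated based on the primary outcome measure (6MWT"), using a 29.4 m mean difference from prehabilitation versus standard care, an SD of about 101.6 m, d = 0.29, alpha 0.05 and 80% power. The result is 54, raised to 70 for 30% dropout. Neither a margin nor the sidedness is stated.

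**Analysis.** The Statistical analysis section plans a mixed model ANOVA, in which a significant time-group interaction shows whether the interventions had the desired effect. Two-sided p < 0.05 "will be considered statistically significant, and mean differences (95% CI) will be reported". The analysis is by intention to treat.

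**The concern.** A non-inferiority hypothesis is tested by comparing a confidence limit with a margin fixed in advance. Here the margin is said to exist but is not given, and the success criterion is a significant difference, which answers another question. Failing to find a difference is not evidence that HIIT is no worse by more than a stated amount.

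A trial of this size will probably give wide intervals and p > 0.05. With a non-inferiority hypothesis on record and no margin to check it against, such a result is easily reported as support. The protocol expects its findings to inform prehabilitation guidelines, so an unsupported claim could reach practice.

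A later SAP cannot fully cure this. The protocol asserts that the margin is already fixed, and it has set the sample size without one.

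**Working it through.** **Inputs.** SD 101.6 m, difference 29.4 m, 80% power, 35 per arm and 30% dropout come from Sampling and Size Calculation; two-sided 0.05 comes from Statistical analysis. Expected analysed numbers run from 70 (no loss) to 70 × 0.70 = 49. The calculation is a two-sample comparison at one time point. It illustrates the scale and is not the full mixed model over five time points.

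**1. The plan's own figure.** d = 29.4/101.6 = 0.289, as stated. For a two-sided test, n per arm = 2 × (1.960 + 0.842)² × (101.6/29.4)² ≈ 188, or 376 in total. One-sided it is 148 per arm, or 296. The stated 54 is not reproduced either way. It can be reached with a repeated-measures interaction test, but only with inputs the protocol does not state (for example f = 0.145, five time points and a correlation of about 0.54). None of these calculations contains a margin. The step to 70 is 54 × 1.3 = 70.2.

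**2. Precision.** SE = 101.6 × √(2/n per arm).

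| | 70 analysed (35 per arm) | 49 analysed (24.5 per arm) |
|---|---|---|
| SE | 24.3 m | 29.0 m |
| 95% CI half-width (t) | 48.5 m | 58.4 m |

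**3. Chance of p > 0.05 if HIIT is truly 29.4 m worse.** Two-sided power from the noncentral t is about 0.22 (70 analysed) and 0.17 (49). The test is therefore non-significant about 78% and 83% of the time, although HIIT would have lost an amount equal to the whole prehabilitation benefit that the protocol cites.

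**4. Non-inferiority power.** No margin is given, so 29.4 m is an assumption. With a true difference of 0 and one-sided alpha 0.025, power ≈ Φ(29.4/SE − 1.96), which is about 22% (70 analysed) and 17% (49). Other assumed margins with 70 and 49 analysed: 14.7 m gives 9% and 7%; 40 m gives 38% and 28%; 53.3 m gives 59% and 45%.

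**5. Margin testable with 80% power.** (1.960 + 0.842) × SE ≈ 68 m (70 analysed) and 81 m (49).

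**6. Baseline adjustment.** This multiplies the SE by √(1 − r²). The protocol gives no r, so these values are assumptions.

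| r | Factor | Half-width (70 to 49 analysed) | Margin for 80% power (70 to 49 analysed) |
|---|---|---|---|
| 0.5 | 0.866 | 42 to 51 m | 59 to 70 m |
| 0.7 | 0.714 | 35 to 42 m | 49 to 58 m |
| 0.8 | 0.600 | 29 to 35 m | 41 to 49 m |

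Across this range, the margin needed for 80% power stays above 29.4 m.

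**The case against.** A reader might infer several stronger things that the documents do not support.

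- **That a non-significant p-value is the only result that could support the hypothesis.** It is not. A difference significantly favouring HIIT would also support non-inferiority. So could the promised 95% CI, once set against a margin.
- **That the protocol plans to read p > 0.05 as non-inferiority.** It nowhere says so. It ties the desired effect to a significant interaction. The misreading is a risk, not a written rule.
- **That the trial can never address its hypothesis.** The interval will be reported, so a margin and rule fixed before unblinding would allow a valid reading, though probably an inconclusive one.
- **That unequal adherence under intention to treat will push the result towards no difference.** The protocol plans to record adherence but assumes no difference between arms. A supporting per-protocol analysis is also something an SAP commonly carries.
- **That the sizing is two-sided.** Only the analysis is declared two-sided.

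It can also fairly be said that the arithmetic describes a simpler test than the planned mixed model, and that baseline adjustment would improve precision. Both are true, and they limit the figures to an illustration. Neither supplies a margin or a rule, and neither removes the conflict between the hypothesis and the rest of the design.

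**Conclusion.** The point holds as an internal contradiction. The hypothesis is non-inferiority against a margin described as pre-specified but given no value. The objective, sizing and significance criteria are difference-based, and nothing in the protocol tests the hypothesis as worded.

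The size of the problem depends on the protocol's SD of 101.6 m, 49 to 70 analysed, and a single-time-point comparison without baseline adjustment. On that basis the trial would miss a true 29.4 m deficit about four times in five. It would have roughly one chance in five of showing non-inferiority at a 29.4 m margin, and would need a margin of about 68 to 81 m for 80% power. The 29.4 m reference comes from prehabilitation versus standard care. The protocol does not establish it as the MICT effect, so using it as a margin or a ceiling is an assumption. This should be corrected before unblinding.

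**What to change.** **Preferred.**
- Delete the non-inferiority wording from the Introduction and section 1.4.
- State an estimation question for both primary outcomes, 6MWT and MIP: HIIT minus MICT with a 95% CI.
- Add that p > 0.05 will not be read as non-inferiority or equivalence.
- In Sampling and Size Calculation, replace the 80% power claim with the power for the planned 70. For 29.4 m in the simple comparison above, that is about 22% with no loss and 17% with 49 analysed.

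**If non-inferiority is kept.**
- Before unblinding, state and justify a numerical margin for 6MWT and for MIP, or name one of them as the sole primary outcome.
- Conclude non-inferiority only if the lower limit of the two-sided 95% CI for HIIT minus MICT lies above minus the margin.
- Add a supporting per-protocol analysis, and state the actual power for the chosen margin.
- If 29.4 m is used as a ceiling for the margin, label it as an assumption.

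**Cost.** The preferred route needs a protocol amendment with ethics and registry notification, and no new data. It gives up a claim that the trial is poorly placed to support, and it makes the low power explicit. Keeping non-inferiority with 80% power would cost far more: at a 29.4 m margin and without baseline adjustment, 188 per arm, or 376 analysed, and 376/0.70 ≈ 538 recruited.

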## **Literature Review**

Abdominal surgery is the most common surgery performed worldwide. Major abdominal surgery is conducted under general anaesthesia and involves making an incision into the abdominal cavity with manipulation of the internal organs, typically requiring at least an overnight hospital stay (Donati et al., 2004). Physiotherapists studying this population often classify abdominal surgeries based on the size and location of the abdominal incision(s) (Reeve, 2016). Under this definition, major abdominal surgery encompasses gastrointestinal, hepatobiliary, colorectal, urological, vascular, and

gynaecological procedures performed via open or minimally invasive abdominal approaches, but generally excludes laparoscopic surgeries where the total incision length is less than 5 cm

Mounting evidence has firmly established that low levels of cardiorespiratory fitness (CRF) are associated with a high risk of cardiovascular disease, all-cause mortality, and mortality rates attributable to various cancers. Recent studies suggest that in addition to being a strong predictor of cardiovascular and all-cause mortality in both asymptomatic and clinically referred populations, CRF could be especially helpful in the preoperative risk assessment of patients undergoing cardiovascular and noncardiovascular surgery, predicting surgical complications and short-term outcomes in patients subjected to abdominal aortic aneurysm repair, hepatic transplantation, lung cancer resection, upper gastrointestinal surgery, intra-abdominal surgery, bariatric surgery, and coronary artery bypass grafting. In addition, when patients with coronary artery disease who had to wait in the hospital for coronary artery bypass grafting were randomized into an exercise training group, outcomes were superior to those in the standard care group, because of a reduced rate of postoperative complications and shorter hospital stays were observed (Ross 2016)

Early Recovery after Surgery (ERAS) is a multi-model care pathway that reduces stress response to surgery and tries to accelerate post-op recovery. ERAS is managing the patient preoperatively, through the Operation and post-operatively. Enhanced recovery after surgery (ERAS) is a combination of perioperative care components built upon a multimodal approach that integrates evidence-based interventions to reduce convalescences across multiple surgical procedures. Since ERAS was first implemented within hospitals over twenty years ago, post-surgical outcomes have improved for patients (Kehlet and Wilmore 2008). Length of stay has decreased, with no subsequent increase in readmission rates (Paton et al. 2014), with concurrent improvements in clinical outcomes whilst having a beneficial impact on healthcare resources. ERAS programmes are supported by evidence-based preoperative, intraoperative and postoperative procedures to accelerate the achievement of discharge criteria. ERAS originated in elective colorectal surgery but has spread to other surgical subspecialties, including, but not limited to, gastrointestinal, hepatobiliary, orthopaedic, cardiac, thoracic, head and neck, breast and gynecologic surgery (Koci'an P 2023)

The role of physiotherapy within ERAS pathways is important in both preoperative and postoperative routines (Carli et al. 2010). Implementing a preoperative strength programme has been shown to promote musculoskeletal improvements in preparation for a forthcoming physiological stressor, and is an emerging key component of ERAS (Carli et al. 2010). A literature review found preoperative exercise in patients scheduled for cardiovascular, thoracic, abdominal and major joint

replacement surgery to be well-tolerated and effective (Hoozeboom et al. 2014). Postoperative exercise programmes are also recommended by ERAS guidelines, promoting muscle hypertrophy and the return to function after major surgery (ERAS Society 2017).

The standard prehabilitation program may include aerobic exercise which often moderate-intensity continuous training (MICT) is used to improve cardiovascular fitness (Moran et al 2016), resistance training to strengthen muscles and improve overall physical function (Carli et al 2010), breathing exercise to enhance lung capacity and respiratory muscle strength (Weiner et al 2002), and education with lifestyle counseling includes guidance on smoking cessation, nutrition, and overall physical activity (Barberan-Garcia et al. 2014)

A research done by Steffen et al. (2023), the preoperative exercise and education program will be delivered 4-8 weeks before surgery and include up to 24 sessions with 50 minutes per session with supervised, high-intensity training. Individualised exercise prescription, progression, and follow-up with a local physiotherapist or exercise physiologist up to 32 sessions for 30 minutes while unsupervised home exercise, up to 56 walking sessions for 30 minutes had been delivered plus advice to walk continuously for 30 minutes daily. Pablo et al (2023) concluded that prehabilitation programmes with more than one supervised session per week improved physical function but did not enhance surgical outcomes.

Inspiratory muscle training using an inspiratory threshold loading device for 2–4 weeks and indicated before abdominal or cardiac surgery to prevent postoperative pulmonary complications. Clinically significant complications include atelectasis, infection (bronchitis, pneumonia), prolonged mechanical ventilation and respiratory failure, exacerbation of underlying chronic lung disease, and bronchospasm (Katsura 2015). Preoperative inspiratory muscle training reduces the incidence of postoperative pneumonia and atelectasis (risk ratio 0.53; 95% CI 0.34–0.82). It also reduces the length of hospital stay by about one day (MD –1.33; 95% CI –2.53 to –0.13)(Katsura 2015).

A meta-analysis of prehabilitation interventions consisting of inspiratory muscle training, aerobic exercise, and/or resistance training found that prehabilitation decreased post-operative complications after intra-abdominal operations in a traditional surgical care setting (OR 0.59, 95% CI 0.38 to 0.91;  $p=0.03$ ) (Moran 2016).

Chan (2021) proved that preoperative breathing exercises reduced length of stay (LOS), postoperative pulmonary complication (PPC), and pneumonia and potentially improved six minute walking distance (6MWD) in patients undergoing surgical lung cancer resection. Breathing exercises in combination with aerobic exercise yielded greater reductions in LOS. Randomized controlled trials are needed to test the feasibility of introducing a preoperative breathing exercise program in this patient population.

Exercise training is the intervention in this review. Exercise training is "a subset of physical activity that is planned, structured, and repetitive, and has as a final or an intermediate objective, the improvement or maintenance of physical fitness" (Caspersen 1985). This includes aerobic training, resistance training or a combination of these with or without inspiratory muscle training. Exercise training was not commonly prescribed in the preoperative management of people with NSCLC (Cavalheri 2013), possibly due to uncertain evidence of its feasibility and effectiveness (Cavalheri 2020). However, the evidence for the effectiveness of preoperative exercise training in people with NSCLC has substantially grown since the early 2010s. Cochrane Review in 2017, demonstrated initial evidence (low quality) that preoperative exercise training may reduce the risk of postoperative pulmonary complications, intercostal catheter duration and length of hospital stay, and may improve preoperative exercise capacity and forced vital capacity (FVC) (Cavalheri 2017).

Preoperative exercise can reduce postoperative hospital stay, pulmonary, and other complications in abdominal and cardiovascular surgery. PaO2 was significantly increased in the intervention group during the preoperative period following training. Exercise improves inspiratory muscle endurance, functional mobility, reduces postoperative pain scores and anxiety, and improves quality of life (Iqbal 2019). Matassi 2018 indicated that preoperative exercise of the arthritic knee facilitates immediate postoperative recovery following primary total knee replacement. Preoperative exercise therapy might also improve the physical fitness of patients before major surgery, and preoperative chest physiotherapy seems to be effective in reducing pulmonary complications (Pouwels 2014).

Prehabilitation enables patients to withstand the stress of surgery by augmenting functional capacity. Preoperative exercise decreases sympathetic over-reactivity, improves insulin sensitivity, and increases the ratio of lean body mass to body fat. It also improves physical and psychological readiness for surgery, reduces postoperative complications and the length of stay, and improves the

transition from the hospital to the community. A cardiac prehabilitation program should include education, nutritional optimization, exercise training, social support, and anxiety reduction, although current existing evidence is limited. Three non-CS studies have successfully demonstrated the benefits of 3 to 4 weeks of prehabilitation in the context of ERAS. Prehabilitation interventions prior to CS must be further examined to advance this area of research.

Prehabilitation before abdominal surgery has increased in popularity over recent years and aims to improve pre-operative conditioning of patients to improve post-operative outcomes. This is recommended as part of ERAS guidelines. The beneficial effect of such protocols is not well established with conflicting results reported. This review aimed to assess the effect of prehabilitation on postoperative outcomes after major abdominal surgery.

Moderate intensity interval training (MICT) is often chosen as the control in studies comparing different exercise modalities because it is a well-established, evidence-based component of prehabilitation programs. It involves sustained exercise at a moderate intensity, typically around 40-60% of VO2 max, which is safe and effective for improving cardiovascular and respiratory function. MICT is the traditional standard against which newer or alternative interventions, like High-Intensity Interval Training (HIIT), are compared.

MICT is normally has been chosen as a control because MICT has a long history of safe and effective use in various patient populations, including those awaiting surgery. West et al. (2015) demonstrated in a randomized controlled trial that MICT improved preoperative fitness levels and reduced postoperative complications in high-risk surgical patients. The study supported the use of MICT as a safe and effective intervention in prehabilitation. Besides that, it provides a baseline against which the benefits of more intense or novel interventions can be measured. In a systematic review, Hulzebos et al. (2012) used MICT as the control intervention to compare the effects of different preoperative exercise regimens. The study found that MICT consistently provided a reliable baseline for comparing the benefits of more intensive or alternative exercise programs. Furthermore, patients are generally more familiar with moderate-intensity exercise, which may lead to higher compliance rates in a clinical setting. A study by Lee et al. (2018) found that patients were more likely to adhere to MICT regimens due to their familiarity with moderate-intensity exercise. The

study emphasized that patient compliance is higher when the exercise intensity is perceived as manageable, making MICT a suitable control in prehabilitation studies.

High-intensity interval training (HIIT) is a bolus-dosing approach that efficiently increases Cardiorespiratory fitness and is feasible in most surgical populations. High-intensity interval training involves repeated aerobic high-intensity intervals at approximately 80% of the maximum heart rate, followed by active recovery. The rapid increases in CRF elicited with HIIT is appealing for preoperative patients, and in the context of pathology, age, and comorbidities, the volume of training stimulus required to improve CRF can often be achieved.

HIIT provide advantages more in term of time efficiency, greater improvement in cardiorespiratory fitness, improves metabolic health and more effective in preserving muscle mass. A study by Gillen et al. (2016) demonstrated that HIIT, which required significantly less time than MICT, produced similar improvements in cardiovascular and metabolic health. The study highlighted the time-efficiency of HIIT as a major advantage for patients with limited time before surgery.

The study by Weston et al. (2014) showed that HIIT led to greater improvements in VO2 max compared to MICT in patients with cardiovascular disease. Since VO2 max is a critical measure of cardiorespiratory fitness, HIIT's superior results suggest its potential advantage in prehabilitation.

Besides that, A meta-analysis by Jelleyman et al. (2015) concluded that HIIT was more effective than MICT in improving insulin sensitivity and reducing abdominal fat. These findings are particularly relevant for patients with metabolic conditions awaiting surgery. While, a study by Robinson et al. (2017) found that HIIT was more effective in preserving muscle mass in older adults compared to MICT. Muscle preservation is crucial for patients undergoing major surgery, as it can impact postoperative recovery and physical function.

In a systematic review and meta-analysis by Clifford (2023), pooled results indicated several positive associations of HIIT vs standard care with CRF or postsurgical outcomes. These findings suggest that HIIT may improve patient outcomes, with robust benefits across patient populations (Clifford et al. 2023) . Preoperative HIIT shows promising results and should be included in prehabilitation programs. The high degree of heterogeneity in our analysis demonstrates differences

in training programs and supports the need for further well-designed studies to improve the quality of evidence

| Author                  | Population                                    | Findings                                                                                                                                                                                                                                                                                                                                      | Intervention                                                                                                                                                                                                                                                                                                                                                                             | Outcome measure                                                                                                                                                 | Gap                                                                                                                                   |
|-------------------------|-----------------------------------------------|-----------------------------------------------------------------------------------------------------------------------------------------------------------------------------------------------------------------------------------------------------------------------------------------------------------------------------------------------|------------------------------------------------------------------------------------------------------------------------------------------------------------------------------------------------------------------------------------------------------------------------------------------------------------------------------------------------------------------------------------------|-----------------------------------------------------------------------------------------------------------------------------------------------------------------|---------------------------------------------------------------------------------------------------------------------------------------|
